#### Qualitative interviews

Following recruitment, patient interviews will be conducted with a sample of 15 participants after the 12-week intervention. The purpose of these interviews is to gather valuable insights and perspectives regarding the study and the intervention. Topics covered will include the participants’ acceptance of the technology, factors influencing their participation in the trial, any unexpected benefits or adverse effects experienced, as well as their experiences with pain and any impact on their overall function and exercise. Interviews will last between 30 and 45 min. The audio files will be transcribed verbatim by a professional transcription company. The data will be analysed using thematic analysis and NVivo software will be used to manage the data analysis.

### Intervention

The intervention is SPIN-VR that consists of five biomechanically validated Movella Dot IMUs (Movella), which are positioned on the upper and lower limbs in accordance with the movement requirements of each virtual exercise. Sensor placement is task specific to ensure accurate motion capture and feedback during exercise performance. The games will be played on a laptop computer that can be connected to a TV to enable a larger view of the gaming environment. Connecting it to a TV is optional. Each participant will be provided with a unique login to the VR software, which will allow the research team to track the regularity of use and progress of all study participants. This will allow the research team to determine adherence with the SPIN-VR programme such as how often and for how long participants are using the system for each exercise.

Participants will be asked to do the exercise programme three times a week for 12 weeks at home. At the end of these 12 weeks, they will be asked to return for the first follow-up visit and to return the equipment. Patients can continue to perform the exercises they learnt without the SPIN-VR. To personalise the SPIN-VR games and set the optimal difficulty level for each participant, the system allows adjustments based on factors such as the number of obstacles, speed, repetitions, range of motion and dual-tasking complexity. The games included in the SPIN-VR replicate the following exercises:

Weight shifting (shifting weight in the hips).Lunging/step forward (placing one leg forward and applying weight to it).Stand up and sit down (standing upright from a seated position in a chair).High stepping (lifting each knee up and down).

The games will be progressed during the 12 weeks if participants scored above a threshold on a composite total score so they can progress to more advanced tasks. On a weekly basis, the participant and physiotherapist can have access to a report on performance and number of times and for how long the participant has interacted with the system. The individual will continue to do the SPIN-VR programme and will have the option of scheduling up to two appointments during the 12 weeks with their physiotherapist.

### Comparator

The comparator is standard physiotherapy care that will consist of an initial assessment and follow-on face-to-face or remote follow-up sessions with the physiotherapist as is normally delivered within the physiotherapy service. Usual care treatment will be physiotherapy advice and exercise^48^ as decided by the treating physiotherapist.

### Recruitment

Participants will be identified by a member of the clinical physiotherapy team in outpatient clinics in the University Hospital of Wales in Cardiff. Patients from the waiting list for physiotherapy care, and those already attending musculoskeletal clinics, will be screened. They will be screened for eligibility against the eligibility criteria, and if they are interested, they will be offered a participant information sheet. Contact details will be obtained and passed on to the research team, who will then approach participants to arrange a baseline assessment and informed consent visit. A copy of the consent form is attached in the online supplemental material. Consent to share patient contact details with the research team will be obtained beforehand.

### Randomisation and blinding

Randomisation will be provided via a computer-generated list. The research team will access the web-based randomisation module and enter the required data and confirmation of patient eligibility and consent. Allocation is concealed until randomisation is complete and irreversible within the system. The researcher can then inform the participant of their allocation. Because of the nature of the intervention, patients and members of the research team will not be blinded to study allocation.

### Safety

The physical component of the intervention does not differ from what a patient would be expected to do in usual care physiotherapy. Therefore, it poses a minimal risk. For this study, serious AEs that are related to the intervention and unexpected events occurring from the time of randomisation until the participant’s 24-week follow-up will be recorded. AEs will be recorded through standard data collection.

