**Method and analysis:**

This single-centre, open-label, randomised controlled feasibility trial will evaluate the SPIN-VR system over 12 weeks compared with usual care physiotherapy for knee OA. 50 participants will be randomly assigned to either the SPIN-VR or usual care group, with follow-ups at 12 and 24 weeks post randomisation. The primary outcomes will be a description of feasibility of recruitment, patient willingness to be randomised, the completeness of outcome measures and patient adherence to the intervention. Secondary outcomes include evaluations of muscle strength, endurance, aerobic capacity, exercise technique, central pain processing and self-reported pain mechanisms and moderators. Participants in the intervention arm will be interviewed after 12 weeks to capture their experience in using the VR system.

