### Primary outcome measures

Feasibility of recruitment, measured by enrolling 4 patients per month.Completeness of outcome measures, measured by the number (%) of each questionnaire and mechanistic outcome completed at 12 weeks and 24 weeks post randomisation.Fidelity of healthcare professionals delivering intervention using treatment logs and face-to-face contact, and observation of two assessments and training sessions for setting up patients with knee OA with the intervention.Acceptability of intervention and trial procedures through interviews with patients and staff about expectations and experience of the intervention, and barriers and facilitators to trial participation.Adverse events (AEs) through treatment logs and patient interviews will be used to find issues related to knee symptoms or muscle soreness and falls, and motion sickness, plus any unexpected AEs.Adherence to the intervention by the number of times and date/time of when patients logged in to the VR games and number of physiotherapy follow-up consultations.

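### Adverse events are a primary outcome, but one named source reaches only the SPIN-VR arm as written, and the serious-event recording rule is ambiguous and leaves some events out

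*Protocol article*

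**What the plan says.** All references are to the protocol article.

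- **Primary outcome measures** lists AEs as a primary outcome and names two sources: "Adverse events (AEs) through treatment logs and patient interviews will be used to find issues related to knee symptoms or muscle soreness and falls". Motion sickness and any unexpected AEs are added to the list.
- **Abstract, Method and analysis** places the interviews in one arm: "Participants in the intervention arm will be interviewed after 12 weeks to capture their experience in using the VR system".
- **Qualitative interviews** gives the number and timing: "patient interviews will be conducted with a sample of 15 participants after the 12-week intervention". It does not name an arm. Its topics include "any unexpected benefits or adverse effects experienced".
- **Primary outcome measures** also uses treatment logs to judge delivery of the intervention: "Fidelity of healthcare professionals delivering intervention using treatment logs and face-to-face contact". Whether the same logs are kept for usual care is not stated.
- **Safety** records "serious AEs that are related to the intervention and unexpected events occurring from the time of randomisation" up to the 24-week follow-up. The next sentence says that AEs are recorded through standard data collection and sets no restriction by arm.
- **Study design** and **Sample size** give 50 participants allocated equally. **Trial assessments** gives in-person visits at 12 and 24 weeks. **Data analysis** describes no between-arm comparison of AEs.

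**The concern.** Two stated rules affect what the AE data will be able to show.

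The first is ascertainment. An interview that asks about adverse effects can turn up soreness, knee flares or near-falls that nobody wrote in a log. If one arm has this extra source and the other does not, a difference in counts may reflect how hard the events were looked for. The interviews also come after week 12, while the safety window runs to week 24.

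The second is the serious-AE rule. It applies a judgement of relatedness, and possibly of expectedness, when the event is recorded and not afterwards. The article does not say who makes that judgement. It does say that the research team is not blinded. Relatedness to the intervention is hard to interpret for someone who never received SPIN-VR.

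The Safety section rests its minimal-risk statement on the exercises being no different from usual care, yet the outcome list looks for falls and motion sickness, and the games add obstacles and dual tasks. Per-arm counts gathered in the same way are what would test that premise and inform the definitive trial. A serious event that was never recorded cannot be reassessed later.

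**Working it through.** The article states no AE rate and no AE-based sample size, so there is no figure of its own to reproduce.

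**Interview coverage.** Inputs: 50 participants in equal arms, so 50/2 = 25 per arm (Study design, Sample size), and 15 interviews (Qualitative interviews), all in the intervention arm (Abstract).

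- SPIN-VR: 15/25 = 60%.
- Usual care: 0/25 = 0%.
- Whole trial: 15/50 = 30%.

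**How much this could matter.** The capture rates below are assumptions; the documents give none. Let the true risk be the same in both arms. Let *s* be the chance that logs and routine collection find an AE (the same in both arms), and *i* the chance that an interview finds it, independently of *s*. With 60% of SPIN-VR interviewed, the true risk cancels:

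apparent ratio = [0.6 × (1 − (1 − s)(1 − i)) + 0.4 × s] / s

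| s | i = 0.5 | i = 0.9 |
|---|---|---|
| 0.5 | (0.6 × 0.75 + 0.20)/0.5 = 1.30 | (0.6 × 0.95 + 0.20)/0.5 = 1.54 |
| 0.8 | (0.6 × 0.90 + 0.32)/0.8 = 1.075 | (0.6 × 0.98 + 0.32)/0.8 = 1.135 |
| 1.0 | 1.00 | 1.00 |

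In participants: at an assumed true risk of 20% and s = 0.5, the expected number found in SPIN-VR is 25 × 0.2 × 0.65 = 3.25 (i = 0.5) or 25 × 0.2 × 0.77 = 3.85 (i = 0.9), against 25 × 0.2 × 0.5 = 2.5 in usual care.

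**If routine capture differs by arm.** SPIN-VR participants exercise at home with up to two optional physiotherapist appointments (Intervention). Usual care has sessions as normally delivered (Comparator). If usual care had the better routine capture, say 0.8 against 0.5, the ratio would be 0.65/0.8 = 0.81 (i = 0.5) or 0.77/0.8 = 0.96 (i = 0.9). With the two values exchanged it would be 0.86/0.5 = 1.72 or 0.908/0.5 = 1.82. The direction is therefore not known.

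**The serious-AE rule.** The Safety phrase has two ordinary readings. Set against the four possible classes of serious event:

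| Class of serious event | Must be both related and unexpected | Related serious AEs, plus unexpected events |
|---|---|---|
| Related, unexpected | recorded | recorded |
| Related, expected | not recorded | recorded |
| Unrelated, unexpected | not recorded | recorded |
| Unrelated, expected | not recorded | not recorded |

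The last row falls outside the rule on either reading. For usual care, the first reading would in effect exclude serious events, because relatedness to SPIN-VR can hardly be satisfied there. On the second, unexpected events in usual care are recorded.

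**The case against.** The case on the other side is substantial.

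- **Interviews are not the only source.** Treatment logs are named beside them, and the Safety section's routine recording applies to everyone. A reader might infer that usual-care AEs are not collected, or that nothing is collected after week 12. The documents do not support that: the limits apply to the interviews alone. This stands.
- **The serious-AE rule is not confined to related events.** A reader might infer that a serious event is recorded only if related. The phrase goes on to include unexpected events, and on the two-class reading an unexpected serious event in usual care is recorded. The general sentence on AEs might also catch a serious event as an ordinary AE. This stands, but the article does not say how the two sentences fit together, and the unrelated-and-expected class remains outside the serious-AE rule.
- **Upward bias in the SPIN-VR counts is not shown.** The ratio is 1.00 if routine collection is complete, and greater therapist contact in usual care could push it below 1. This stands.
- **The arm restriction rests on the abstract.** The Qualitative interviews section does not repeat it. Nothing in the article contradicts it, though, and acceptance of the technology is an interview topic.
- **No AE comparison is planned, and 25 per arm would be imprecise anyway.** This is true and limits the consequence. It does not remove the value of collecting a primary outcome in the same way in both arms.
- **A journal article condenses the full protocol.** Form content and AE prompts may well be there, so the lack of an AE checklist in the article is not held against it. The point concerns what the article does state: the sources, who is interviewed, and the recording rule.

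**Conclusion.** The concern holds in a limited form. One of the two sources named for a primary outcome covers, as written, at most 15 of about 25 SPIN-VR participants and no usual-care participant. The resulting distortion is a risk of unknown size and direction. With equal true risk and equal routine capture of between 50% and 100%, the apparent ratio lies between 1.00 and 1.54. Below 50% capture it would be larger, and unequal routine capture could move it either way. These figures rest on assumed capture rates and on all 15 interviewees coming from the SPIN-VR arm.

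The serious-AE wording is the firmer part because it needs no assumption about rates. It is ambiguous, has no clear meaning for usual care, and on either reading omits serious events judged unrelated and expected. Such an omission could not be put right by later adjudication. The documents do not show that any event has been missed, or that the arms' safety data will in fact be incomparable.

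**What to change.** - Reconcile the Abstract, Primary outcome measures, Qualitative interviews and Safety sections: state which arm or arms are interviewed, and which AE sources apply in each arm.
- Ask the same short set of AE questions in both arms at the existing 12- and 24-week visits (knee symptoms, muscle soreness, falls, motion sickness, anything else). Report per-arm AE counts from this common source.
- Report AEs found only through interviews separately.
- Record every serious AE in both arms from randomisation to week 24, then classify relatedness and expectedness. Reword the Safety sentence to match.

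The cost is a short case report form item at visits already planned, slightly more serious-AE recording, and an amendment. No extra visits are needed. If the full protocol and forms already do this, correcting the published wording is enough. Last follow-up is expected at the end of June 2026, so the benefit shrinks with delay: participants past their 12-week visit could be asked the common questions only at 24 weeks.

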### Sample size

This feasibility study aims to recruit and randomise 50 participants, a sample size chosen to provide adequate precision in estimating key feasibility parameters, specifically retention and adherence rates, with a 95% confidence intervals of approximately ±10%.^49 50^ As the primary objective is to evaluate feasibility rather than effectiveness, no formal power calculation was performed.^51^ The sample size was pragmatically determined based on an anticipated recruitment rate of approximately four participants per month over a 13-month period, with an estimated 60% of eligible patients expected to consent to participation. This conservative sample size is intended to generate essential data to inform the design and sample size calculations of a future pilot or definitive RCT.

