## Methods and analysis

### Study design

This is a single-centre, open-label, randomised controlled feasibility trial of a 12-week SPIN-VR programme with a 24-week post-randomisation follow-up. 50 people diagnosed with knee OA who fulfil National Institute for Health and Care Excellence (NICE) and American College of Radiology (ACR) criteria for a knee OA diagnosis^6 35^ will be randomly assigned in equal numbers to either an SPIN-VR programme or to receive usual care physiotherapy.

The study is planned to run from August 2024 to the end of June 2026 when the last patient follow-up is expected.

The study aims to assess the following feasibility outcomes.

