### Data analysis

The main outcome of recruitment feasibility will be reported, as frequency of patients recruited during the study period. Reasons for screening or randomisation failure will be collated and presented as frequencies. Descriptive data will include an evaluation of eligibility, recruitment, acceptability of and adherence to the intervention, with 95% CIs. Secondary outcome measures, including PROMs, will be assessed before and after the intervention to establish any possible trend in the intervention effects over time and understand the variability in data. The completion of outcome measures will be reported and changes in outcome assessments relative to baseline assessments will be analysed using appropriate parametric or non-parametric statistics based on the characteristics of the data. All tests will be two-sided with an alpha level of 0.05. Estimates of population variances of outcomes for future power calculations will use the upper 80th percentile of confidence intervals around the estimates will be carried out. In addition, individual performance and movement quality in the VR intervention will be monitored and measured during the 12-week programme, every time the patient completes a training session, to determine any improvement in comparison to baseline measurements.

The qualitative interviews will be used to obtain views on participants’ acceptance of the technology, factors influencing their participation in the trial, any unexpected benefits or adverse effects experienced, as well as their experiences with pain and any impact on their overall function and exercise. Data will be managed using NVivo software. Data will be analysed using Braun and Clarke’s thematic analysis.

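### The stated precision of about ±10 points does not hold for adherence, which is measured only in the 25 SPIN-VR participants; read as a proportion, it has a half-width of about ±12 to ±20 points for rates of 50% to 90%

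*Protocol article*

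**What the plan says.** The Sample size section sets the target: "This feasibility study aims to recruit and randomise 50 participants". It says this number was chosen for adequate precision on two parameters, "specifically retention and adherence rates, with a 95% confidence intervals of approximately ±10" per cent. It assumes no rate for either parameter and names no denominator. The one rate it gives, "with an estimated 60% of eligible patients expected to consent to participation", concerns consent. The section also gives a pragmatic basis, about four participants a month over 13 months (4 × 13 = 52).

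Three other sections fix who contributes adherence data:

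- **Study design:** participants "will be randomly assigned in equal numbers to either an SPIN-VR programme or to receive usual care physiotherapy", so 25 per arm.
- **Primary outcome measures:** "Adherence to the intervention by the number of times and date/time of when patients logged in to the VR games", together with the number of physiotherapy follow-up consultations.
- **Intervention:** each SPIN-VR user has an individual login to the software. Of the tracking that this permits, the article says "This will allow the research team to determine adherence with the SPIN-VR programme".

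The Data analysis section plans to report "acceptability of and adherence to the intervention, with 95% CIs".

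**The concern.** The precision sentence treats retention and adherence as if both were estimated from the same number of people. Usual-care participants have no VR login, so adherence to the intervention can be observed in only half of those randomised. Halving the denominator widens a 95% interval by a factor of √2, about 1.41.

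Adherence is a primary outcome, and the Abstract and Introduction present poor adherence to physiotherapy as the problem that SPIN-VR is meant to address. The sample is also intended to inform the design of a later pilot or definitive trial. A reader planning that trial would expect adherence to be known to about ±10 points, when the likely uncertainty is appreciably larger.

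**Working it through.** **Inputs.** 50 randomised (Sample size); equal allocation, so 25 in SPIN-VR (Study design); adherence measured by VR log-ins (Primary outcome measures, Intervention); 95% confidence, z = 1.96. The article states no expected retention or adherence rate, so the rate p is varied as an assumption.

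**Formula.** The half-width of a 95% interval for one proportion (Wald) is h = 1.96 × √(p(1 − p)/n).

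**Step 1: reproduce the plan's figure with n = 50.** At p = 0.85, h = 1.96 × √(0.1275/50) = 0.099. So ±10 points is recovered for 50 people when the rate is about 85%.

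**Step 2: compare the two denominators.**

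| Assumed rate | Retention, n = 50 | Adherence, n = 25 |
|---|---|---|
| 50% | ±13.9 | ±19.6 |
| 70% | ±12.7 | ±18.0 |
| 80% | ±11.1 | ±15.7 |
| 85% | ±9.9 | ±14.0 |
| 90% | ±8.3 | ±11.8 |

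For example, adherence at 80%: 1.96 × √(0.16/25) = 1.96 × 0.08 = 0.157.

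**Step 3: find the rate at which h = 0.10.** Solve p(1 − p) = n × (0.10/1.96)² for the upper root.

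- n = 50: p(1 − p) = 0.130, so p = 0.846.
- n = 25: p(1 − p) = 0.065, so p = 0.930.

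The formula is symmetric, so a rate of 7% or less would also give ±10 with 25 people.

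**Step 4: check other interval methods for n = 25.** The Wilson half-width runs from ±18.3 points at 50% to ±12.2 at 90%. The exact half-width is ±20.5 at 12/25, ±16.9 at 20/25 and ±14.3 at 22/25. The choice of method does not bring adherence to ±10 over this range.

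**Step 5: alternative reading, adherence as a mean.** The programme is three sessions a week for 12 weeks, or 36 sessions. If adherence is the mean share of these completed, the half-width is 1.96 × SD/√25. The article gives no SD, so these values are assumptions:

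| Between-person SD (points) | Normal | t-based |
|---|---|---|
| 20 | ±7.8 | ±8.3 |
| 25 | ±9.8 | ±10.3 |
| 30 | ±11.8 | ±12.4 |

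On this reading ±10 is met if the SD is about 25 points or less.

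**The case against.** The strongest reply is that the article never defines adherence as yes or no. It lists counts and dates of log-ins and sets no threshold that makes a participant adherent. A mean share of sessions completed is a natural summary, and ±10 points is then attainable with 25 people. This stands as a limit: the figures for 25 people in Step 2 apply to adherence read as a proportion. It does not remove the point. The article calls both parameters rates and attaches one figure to both, and the alternative needs an SD that it does not supply.

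A second reply is that adherence also counts physiotherapy consultations, which usual-care patients attend too. But the outcome is adherence to the intervention, and log-ins exist in one arm only, so 25 remains the denominator.

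A third reply is that the observed interval will be reported in any case, and that no progression rule in the article uses ±10. This is correct and limits the harm. The error lies in what the design is said to deliver and does not carry into the planned analysis.

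A reader might also infer stronger points that the article does not support:

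- **That the retention precision is wrong too.** It is not: ±9.9 at 85% and ±11.1 at 80% both fit an approximate ±10. An unstated assumed rate is the kind of detail a condensed article may leave to the full protocol.
- **That 50 participants has no other justification.** The same section also rests on the recruitment rate.
- **That retention goes unmeasured because the primary outcomes do not name it.** Completeness of each questionnaire and mechanistic outcome at 12 and 24 weeks largely covers it.

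**Conclusion.** The single figure of about ±10 points does not hold for adherence read as a proportion. With 25 people the half-width is about ±20 points at 50%, ±18 at 70%, ±16 at 80% and ±12 at 90%, which is roughly 1.2 to 2 times the stated value. Only adherence of about 93% or more would make the statement true at a plausible level. The article offers no basis for that rate, and its own rationale describes adherence to physiotherapy as poor. Nor does a shared assumption rescue the sentence: the 85% that makes it right for retention gives ±14.0 for adherence.

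The conclusion rests on 25 participants in SPIN-VR, all of them counted, and on adherence being a proportion. If it is a mean share of sessions, the stated figure may be attainable, but that depends on an SD the article does not give. The finding does not show that 50 is too few for a feasibility study.

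**What to change.** Keep 50 participants. In the Sample size section, replace the single figure with one for each parameter, giving the denominator and assumed rate. For example: retention, about ±10 points at 85% of 50; adherence, about ±16 points at 80% of the 25 in SPIN-VR, and at worst about ±20. The assumed rates here are illustrations, to be replaced by the investigators' own expectations.

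If adherence is to be the mean share of the prescribed sessions completed, say so, state the assumed between-person SD, and derive the precision from that SD with 25 people.

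The cost is a less favourable stated figure for adherence if it is a proportion. No extra patients, no new data collection and no change to the primary outcomes are required.
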